## 3. Biological Mechanisms of Ozone Therapy

OT exerts its biological effects primarily through the controlled generation of reactive oxygen species (ROS) and lipid peroxides (LOPs) upon contact with biological fluids. These molecules act as secondary messengers, triggering redox-sensitive signaling pathways such as Nrf2/Keap1/ARE, which upregulate antioxidant defenses and restore redox homeostasis. The hormetic response to low-dose ozone is characterized by a transient, moderate oxidative stress that stimulates cellular adaptation without causing cytotoxicity [29,30,31,32,33].

OT enhances microcirculation and tissue oxygenation by improving rheological properties of blood, increasing erythrocyte flexibility, and promoting oxygen release to hypoxic tissues. Clinical studies have demonstrated increased tissue oxygenation following systemic ozone administration, particularly in ischemic conditions [34,35].

The anti-inflammatory and immunomodulatory properties of ozone are mediated by downregulation of pro-inflammatory cytokines (e.g., TNF-α, IL-1β) and upregulation of anti-inflammatory mediators. Ozone modulates immune cell function, including regulatory T lymphocytes, and shifts cytokine profiles toward an anti-inflammatory state. This is achieved through redox signaling and direct effects on immune cell populations [10,36,37].

Emerging preclinical evidence suggests that ozone therapy, especially via rectal insufflation or ozonated water, can directly and indirectly impact the gut microbiota. Ozone administration has been shown to increase the abundance of beneficial bacteria (e.g., Lactobacillus, Bifidobacterium), restore microbial diversity, and modulate microbial metabolites such as SCFAs and tryptophan derivatives. These changes contribute to improved intestinal barrier function and reduced inflammation in models of atherosclerosis and sepsis [12,13,38].

Overall, OT acts as a redox bioregulator, with pleiotropic effects on cellular signaling, tissue oxygenation, inflammation, immune modulation, and the gut microbial ecosystem [39].

The proposed rectal ozone therapy protocol utilizes concentrations and volumes consistent with established clinical practice, typically ranging from 10 to 40 μg/mL and 180 to 300 mL per session, with gradual titration based on patient tolerance. These parameters have demonstrated safety and efficacy in oncological patients, including those with refractory pelvic toxicity and QT-induced neuropathy, with no serious adverse events reported and only transient meteorism as a minor side effect [40,41,42,43,44]. The impact of ozone on gut microbiota in this context remains unexplored and is a novel focus of the present study.

## 4. Evidence Linking Ozone Therapy to Microbiota Modulation

A growing, yet still nascent, body of research suggests that one of the mechanisms of action of Medical OT may be through the modulation of the gut microbiota. The proposed hypothesis is grounded in ozone’s fundamental principle of hormesis: a low, precise concentration induces a transient, controlled oxidative stress that triggers a beneficial adaptive response in tissues [29,33]. This response is characterized by the activation of the Nrf2 pathway—a master regulator of antioxidant cellular defense—and the concurrent inhibition of the pro-inflammatory NF-ĸB pathway [10,36,37].

When applied via rectal insufflation, this hormetic effect is postulated to rebalance the gut ecosystem through several interconnected mechanisms. The controlled oxidative stress may exert a selective antimicrobial effect, inhibiting opportunistic, pro-inflammatory pathobionts that thrive in the dysbiotic environment created by RT/CT [10,29]. Simultaneously, by attenuating local inflammation and oxidative stress, OT helps restore the mucosal microenvironment, making it more favorable for the recovery of beneficial commensal bacteria, particularly SCFA producers [12,13]. Furthermore, the trophic and reparative effects of ozone on the damaged intestinal epithelium could enhance barrier function, reducing bacterial translocation and subsequent systemic inflammation. Ultimately, this “weeding and seeding” of the gut lumen favors the growth of a healthier, more resilient microbiota [38,45].

### 4.1. Preclinical Data: Insights from Animal Studies

Preclinical evidence linking OT to modulation of the gut microbiota is robustly supported by controlled animal studies using rectal ozone insufflation. In a murine model of atherosclerosis, rectal OT led to significant shifts in the gut microbiome, notably increasing the abundance of beneficial genera such as *Lactobacillus* and *Bifidobacterium*, while reducing pro-inflammatory taxa. These microbial changes were accompanied by increased levels of SCFAs (propionic and butyric acid) and decreased levels of harmful metabolites Trimethylamine (TMA) and Trimethylamine N-oxide (TMAO), suggesting a shift toward an anti-inflammatory gut environment [12].

Further evidence indicates that rectal ozone insufflation reverses sleep deprivation-induced dysbiosis, normalizing the Firmicutes/Bacteroidetes ratio and the abundance of Bacteroides, which is associated with reduced inflammation and improved cognitive function. This effect is linked to the restoration of the intestinal barrier and a reduction in pro-inflammatory cytokines in the colon and brain [46]. Additional animal studies using ozone water enemas in mice transplanted with fecal microbiota from COVID-19 patients demonstrated that OT improved gut dysbiosis, enhanced intestinal barrier function, and reduced systemic inflammation. These effects were mechanistically linked to activation of the SIRT1-Nrf2/HO-1 pathway, providing direct experimental support for the immunoregulatory and antioxidant impact of ozone on the gut ecosystem [13].

Collectively, these studies demonstrate that OT, particularly via the rectal route, induces favorable changes in the diversity and composition of the gut microbiota, restores barrier function, and reduces inflammation, with effects that depend on the pathological context and the initial microbial profile (Figure 1) [12,13,46].

### 4.2. Emerging Clinical Observations and the Current Knowledge Gap

Despite the compelling preclinical rationale and the long-standing clinical use of rectal ozone (dating back nearly 90 years), direct evidence of its impact on the human gut microbiota remains a significant and original area of inquiry. In the oncology context, it is recognized that the gut microbiota influences immune response, inflammation, and the efficacy and toxicity of antineoplastic treatments [47,48]. However, clinical studies directly evaluating the effect of OT on the microbiota in cancer patients are scarce and, to date, no controlled trials demonstrating specific microbial changes following ozone administration have been published.

In other medical areas, such as rheumatoid arthritis and inflammatory diseases, clinical reports and reviews suggest that OT can induce an immunomodulatory and antioxidant response, which might be mediated, in part, by an interaction with the microbiota [49,50]. Nevertheless, robust data confirming microbiota changes in humans after OT are not yet available. This critical gap in knowledge underscores the novelty and relevance of the present project, which aims to be the first to prospectively investigate whether the documented clinical benefits of rectal ozone in patients with chronic pelvic toxicity are indeed mediated through a beneficial modulation of the gut microbiota.

## 5. Proposed Clinical Study/Protocol

Study Population. Primary Cohort (Group R/CIPT, Radiotherapy/Chemotherapy-Induced Pelvic Toxicity): Adult women (≥18 years) with gynecological malignancies (cervical, endometrial, vulvar, vaginal) who have received pelvic RT with/without CT and present with chronic pelvic toxicity (≥3 months duration) rated as Grade ≥2 according to the Common Terminology Criteria for Adverse Events (CTCAE) v5.0 from the U.S. National Cancer Institute. In our institution, these patients are usually referred for compassionate OT due to symptoms refractory to conventional treatment. Control Cohort: Gynecological cancer patients matched by age (±5 years) and primary tumor location, treated with R/CIPT but without symptoms of pelvic toxicity.

Intervention: Rectal Ozone Insufflation +/− direct local application to the affected mucosa (rectal, vesical, and/or vaginal), based on the standard treatment protocol of the Chronic Pain Unit for compassionate use of OT. Proposed Regimen: It usually consists of 40 sessions administered over 4 months, following the unit’s standard operating procedures. The ozone concentration (µgO_3_/mLO_2_) will start at 10 µg/mL and increase by 5 µg/mL every 2 sessions until it reaches 30 µg/mL by the 9th session, after which it will be maintained until week 16. The volume will start at 180 mL and will be progressively increased to 300 mL if tolerated. The total ozone dose will range from 1800 µg to 9000 µg. To address standardization, the rectal ozone insufflation procedure will use a sterile, flexible catheter (14–16 Fr, 20–25 cm), inserted 7.5–12 cm into the rectum after lubrication. The patient will be positioned on their side, and the oxygen-ozone mixture will be administered over 5 min. All procedures will follow the unit’s standard operating protocols and be performed by trained staff. This approach is supported by published clinical protocols and safety data [51].

Inclusion Criteria for all study participants: (1) Adult women (≥18 years of age) with a histologically confirmed gynecological malignancy (cervical, endometrial, vulvar, or vaginal), of any stage, who have completed a course of pelvic RT and/or CT. (2) Ability to understand and willingness to sign the study-specific Informed Consent Form. Additional criteria for inclusion in the OT Group: Presence of chronic R/CIPT, with a duration of ≥3 months following conventional symptomatic management. A toxicity grade of 2 (moderate symptoms; limiting instrumental activities of daily living) or higher, as per the CTCAE v5.0.

Exclusion Criteria for all study participants: any of the following will preclude inclusion: (1) Failure to meet all the inclusion criteria specified above. (2) Unwillingness or inability to provide written informed consent for study participation. (3) Presence of active inflammatory bowel disease (e.g., Crohn’s Disease, Ulcerative Colitis) or a history of major gastrointestinal resection (excluding appendectomy) that could significantly alter gut anatomy and microbiota. (4) Any uncontrolled intercurrent illness or psychiatric condition that, in the investigator’s opinion, would limit compliance with study requirements or interfere with the interpretation of results.

Withdrawal Criteria. Participants will be withdrawn from the study under the following circumstances: (1) Voluntary Withdrawal: At the patient’s own request, at any time and for any reason, without any penalty or impact on their future clinical care. (2) Loss to Follow-up: Inability to contact the patient or their failure to attend scheduled study visits. (3) Clinical Decision: Withdrawal by the principal investigator due to the occurrence of an adverse event, intercurrent illness, or any other clinical reason that justifies discontinuation for the patient’s well-being or the integrity of the study. (4) Protocol Violation: Significant deviation from the study protocol.

All patients, regardless of their decision to participate, decline, or withdraw from the study, will continue to receive standard oncological care and follow-up from their treating physicians. Withdrawal from the study will not affect their access to routine or compassionate medical treatments, including ozone therapy if clinically indicated.

Microbiological & Biomarker Endpoints: Primary Microbiological Endpoint: Changes in gut microbiota composition and diversity. Method: 16S rRNA gene sequencing (Illumina MiSeq platform) of stool samples. Analysis: Differential abundance of key taxa (e.g., Faecalibacterium, Roseburia, Akkermansia vs. Proteobacteria), and alpha/beta-diversity indices. Biomarker Endpoints: Serum samples will be cryopreserved at −80 °C in a registered biobank for subsequent batch analysis of inflammatory cytokines and oxidative stress markers.

Clinical Endpoints: Primary Clinical Endpoint: Pelvic and gynecological toxicity grade measured by: (1) CTCAE v5.0 scale, and (2) EORTC QLQ-CX24 module (cervical cancer-specific). Secondary Clinical Endpoints: (1) Quality of Life (QoL) measured by: EORTC QLQ-C30 (for cancer patients) and EQ-5D-5L™ (for the general population), (2) Psychological Status: Hospital Anxiety and Depression Scale (HADS), and (3) serum inflammatory/oxidative stress biomarker analysis.

Methodology: Sampling Schedule, Assays, and Statistical Approaches. Study Design: Prospective, observational study. Sample Size: 38 patients (19 with toxicity and OT, 19 matched controls without toxicity). Sampling Schedule: (1) R/CIPT Group: Baseline (pre-ozone) and post-treatment (after the final ozone session). (2) Control Group: A single time point during a routine follow-up visit.

Assays: Microbiota: Stool samples for DNA extraction and 16S rRNA sequencing. Inflammatory cytokines and oxidative stress markers: serum samples. The researchers analyzing the stool and serum samples will be blinded regarding the sample’s group assignment (non-toxicity control, pre-ozone, post-ozone).

The analysis of serum biomarkers will encompass a comprehensive panel to evaluate both oxidative stress and inflammatory status. 1. Oxidative Stress Biomarkers: The assessment will include global oxidative stress markers such as FRAP (Ferric Reducing Ability of Plasma), which measures antioxidant capacity; dROMs (Reactive Oxygen Metabolites), which determines the peroxidation potential; and BAP (Biological Antioxidant Potential). Specific molecular biomarkers will also be quantified, including the activity of the key antioxidant enzymes Superoxide Dismutase (SOD) and Catalase (CAT), the levels of reduced glutathione (GSH) as a critical cellular antioxidant, Advanced Oxidation Protein Products (AOPP) as a marker of protein damage, and ROOH (Total Hydroperoxides) to assess the primary oxidation products of lipids and other molecules. 2. Inflammatory Biomarkers: The inflammatory profile will be characterized by measuring a panel of Pro-inflammatory Cytokines: Tumor Necrosis Factor-alpha (TNF-α), Interleukin-6 (IL-6)**,** Interleukin-1 beta (IL-1β), and Interleukin-8 (IL-8/CXCL8)**.** Furthermore, systemic inflammation will be evaluated through established clinical markers: C-Reactive Protein (CRP) and VES (Erythrocyte Sedimentation Rate)**.**

Statistical Approaches: Primary Analysis: Non-parametric tests will be used due to the small sample size (Wilcoxon signed-rank for pre/post ozone, Mann–Whitney U for inter-group comparisons). Spearman correlations for microbiota-clinical parameter associations. All variables will be described as medians and quartiles 1–3 (percentiles 25–75%). *p*-values less than 0.05 will be considered significant, and all hypothesis tests will be conducted two-sided. Software: R (v4.5.0 or higher).

This study is the first to prospectively explore the novel hypothesis that the clinical benefits of rectal OT for chronic R/CIPT could be mediated, in part, through gut microbiota modulation. The proposed mechanistic pathway is: Ozone → Attenuation of local oxidative stress and inflammation (via Nrf2 activation and NF-κB inhibition) → Restoration of a healthy mucosal microenvironment → Promotion of commensal bacteria (e.g., SCFA producers) and suppression of pathobionts → Improved barrier function and reduced systemic inflammation → Clinical improvement in toxicity and Quality of Life.

This approach is fundamentally different from strategies like generic probiotics, as it does not introduce exogenous species but may instead act by “weeding and seeding” the local environment to favor the regrowth of beneficial autochthonous microbiota. If successful, OT could emerge as a novel, cost-effective modality for managing this devastating complication, potentially used alone or synergistically with targeted prebiotics or probiotics (Table 1).

This initial study has inherent limitations. (1) Its observational design and limited sample size (*n* = 38) prevent definitive causal conclusions. (2) The control group has only a single time point measurement (because a routine follow-up visit will be used). However, this sample should be enough for an initial comparison between patients with or without chronic R/CIPT. (3) The initial microbiota analysis is based on 16S rRNA sequencing. The analysis of microbial metabolites (metabolomics), particularly the measurement of SCFA and other tryptophan derivatives, would be highly interesting in the stool samples. However, due to the pilot nature of the study and the need to first establish whether significant changes exist in the community structure (diversity and differential abundance of key taxa such as Proteobacteria or butyrate producers), we have established 16S sequencing as the initial method of choice and have deferred future multi-omic studies for subsequent investigation, should they be warranted. (4) Main potential confounder factors that could significantly alter gut microbiota will be specifically recorded, such as use of systemic antibiotics within 4 weeks prior to the baseline sample collection, or regular use of probiotics (≥4 times per week) within 2 weeks prior to baseline sampling. However, because this is an “observational study”, no modifications will be made to the patient’s routine management.

To build upon these findings, future directions should include: (1) progressing to a randomized, sham-controlled trial (RCT); (2) incorporating multi-omics approaches like shotgun metagenomics and metabolomics; and (3) exploring the potential for personalized medicine by identifying microbial, inflammatory, and/or oxidative stress biomarkers of treatment response.

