Pelvic RT, used for cancers of the prostate, cervix, uterus, rectum, and anus, directly irradiates the lower GI tract, making it a prime model for studying microbiota disruption. The evidence for dysbiosis is robust and characterized by several consistent patterns:
–Loss of Microbial Diversity: A hallmark of a healthy gut is high species richness (alpha-diversity). Multiple studies have demonstrated a significant and rapid decrease in alpha-diversity in patients undergoing pelvic RT. This loss is considered a sign of ecosystem instability and is strongly correlated with the severity of GI symptoms, particularly diarrhea [18,19].–Shifts in Key Bacterial Taxa. Depletion of Beneficial Genera: There is a consistent and dramatic reduction in beneficial, short-chain fatty acid (SCFA)-producing bacteria. Butyrate producers like *Faecalibacterium prausnitzii* and *Roseburia* spp. are particularly vulnerable. Their loss is directly linked to mucosal barrier breakdown and inflammation [18,20].–Expansion of Pathobionts: Concurrently, there is an increase in opportunistic pathogens and pro-inflammatory bacteria. Commonly reported blooms include *Enterobacteriaceae* (e.g., *Escherichia*, *Klebsiella*) and an increased susceptibility to *Clostridium difficile* infection [21,22].–Dose–Response Relationship: The degree of dysbiosis is often correlated with the radiation dose delivered to the rectum and bowel. Higher doses are associated with more profound microbial shifts and worse clinical toxicity [20].–Persistence of Dysbiosis: Critically, these changes are not always transient. Studies following patients for months after RT have found that microbial diversity and the abundance of key beneficial species often fail to return to pre-treatment levels, suggesting long-term alteration of the gut ecosystem [18].

(c)
*Evidence of Dysbiosis in Patients Undergoing Systemic QT.*

While pelvic RT causes localized damage, systemic chemotherapy affects the entire GI tract. The evidence for QT-induced dysbiosis is equally compelling, though the specific changes can vary based on the chemotherapeutic agent.

Agent-Specific Effects:

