## Figures and Tables

**Figure 1 jcm-14-08015-f001:**
[figure not shown]
Proposed Mechanisms of Rectal Ozone Insufflation in Modulating the Gut Microbiome and Restoring Intestinal Homeostasis. This schematic illustrates the hypothesized pathway through which medical ozone, administered via rectal insufflation, exerts its effects. The core principle is oxidative hormesis, where controlled, low-dose ozone triggers a beneficial adaptive response. The process begins with (1) the local application of ozone in the gut lumen, which induces a mild, transient oxidative stress. This primary event initiates two key parallel mechanisms: (2) the Direct Modulation of the Gut Microbiota, and (3) the Activation of Host Cellular Pathways (Nrf2/SIRT1). These mechanisms converge to (4) Improve Gut Barrier Integrity and (5) Reduce Local and Systemic Inflammation, ultimately leading to the restoration of a healthy gut ecosystem and amelioration of disease symptoms. HO-1: Heme Oxygenase-1; IL-1β: Interleukin-1 beta; IL-6: Interleukin-6; IL-10: Interleukin-10; NF-κB: Nuclear Factor Kappa-Light-Chain-Enhancer of Activated B cells; NLRP3: NLR Family Pyrin Domain Containing 3; Nrf2: Nuclear Factor Erythroid 2–Related Factor 2. QT, Chemotherapy; RT, Radiotherapy; SCFAs: Short-Chain Fatty Acids; SIRT1: Sirtuin 1. TMAO: Trimethylamine N-Oxide; ↑, increase; ↓, Decrease.

**Table 1 jcm-14-08015-t001:** Schematic of the Rectal Ozone Therapy (OT) Clinical Study Design.

Stage	Key Elements	Study Groups & Sampling	Method and Endpoints
Population & Criteria	Objective: Adult women (≥18 years) with gynecological malignancy who have completed pelvic radiotherapy (± chemotherapy).	R/CIPT + OT Group (*n* = 19): With chronic pelvic toxicity (CTCAE ≥ Grade 2, ≥3 months duration). Control Cohort (*n* = 19): No pelvic toxicity, matched by age and tumor site.	Inclusion/Exclusion Criteria: Ensuring exclusion of confounding factors (e.g., active inflammatory bowel disease).
Intervention & Treatment	Intervention: Ozone Therapy (OT) via rectal insufflation with/without direct local application.	OT Group Only: Receives ≈ 40 sessions of OT over 4 months.	Ozone Regimen: Progressive dosing (10 µg/mL up to 30 µg/mL).

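### The toxicity-versus-control microbiota contrast is expected to be partly confounded by radiation dose, because controls are matched only on age and tumor location and the planned test is unadjusted

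*Protocol article*

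**What the plan says.** In the protocol article, section 5 (Study Population), the control cohort consists of "Gynecological cancer patients matched by age (±5 years) and primary tumor location" who have no symptoms of pelvic toxicity. Table 1 repeats the same two factors: "No pelvic toxicity, matched by age and tumor site". The toxicity group must have CTCAE Grade 2 or higher.

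Section 5 (Statistical Approaches) gives "Mann–Whitney U for inter-group comparisons", two-sided at 0.05, and names no covariate. The limitations in the same section say of the single control sample that "this sample should be enough for an initial comparison between patients with or without chronic R/CIPT".

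Section 2, on dysbiosis after pelvic radiotherapy, states that "The degree of dysbiosis is often correlated with the radiation dose delivered to the rectum and bowel" and that "Higher doses are associated with more profound microbial shifts and worse clinical toxicity".

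The confounders to be recorded are illustrated by recent antibiotics and regular probiotics. Radiation dose is not named among the matching factors, the recorded factors or the analysis.

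On prior treatment, section 5 describes the toxicity cohort as women "who have received pelvic RT with/without CT and present with chronic pelvic toxicity". The inclusion criteria for all participants accept women "of any stage, who have completed a course of pelvic RT and/or CT". Table 1 describes the whole population as having completed pelvic radiotherapy, with or without chemotherapy.

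**The concern.** On the protocol's own account, rectal and bowel dose is associated with the outcome of the contrast (the microbiota) and with the variable that defines the groups (toxicity). Choosing controls because they have no toxicity makes a lower average dose among them something to expect, beyond chance imbalance. Matching on tumor location does not settle this: the study admits any stage, and dose can differ within one tumor site.

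The contrast is the stated purpose of the control cohort, which is half the sample (19 of 38). If the toxicity group shows lower diversity or fewer butyrate producers, the planned test cannot tell how much of that goes with chronic toxicity and how much with a higher past dose. Blinding the laboratory does not help, because the imbalance is there before any sample is taken.

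The eligibility wording could widen the gap. Read literally, a control may have had chemotherapy alone and so no pelvic radiation at all.

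**Working it through.** **Is the structure of a confounder present?** Three statements in the article are enough.

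1. Dose and outcome: section 2 says the degree of dysbiosis is often correlated with rectal and bowel dose.
2. Dose and group: section 2 says higher dose goes with worse toxicity, and section 5 forms the groups on toxicity.
3. No control of dose: section 5 and Table 1 match on age and tumor location only, and the test has no covariate.

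Dose also precedes both the toxicity and the stool sample.

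**Which analyses are touched?** Controls give one sample, so they have no change score. The before/after Wilcoxon test compares each treated woman with herself, and her past radiation dose is the same at both times. Only the between-group contrast is exposed.

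**How large could it be?** The article gives no dose figures and no effect size or power for the 38 women, so there is no stated figure to reproduce. For scale, the standardized difference detectable with 80% power at 19 per group is (1.960 + 0.842) × √(2/19) = 0.91, or about 0.91/√0.955 = 0.93 for Mann–Whitney.

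Assumptions for the illustration:
- 19 per group.
- Dose is N(D, 1) in the toxicity group and N(0, 1) in controls.
- Microbiota index = −r × dose + √(1 − r²) × noise, with no direct effect of group.

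The group shift that arises from dose alone is r × D. It runs from 0.3 × 0.5 = 0.15 SD to 0.5 × 1.0 = 0.50 SD.

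Rejection by Mann–Whitney at two-sided 0.05 (4,000 replicates per cell):

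| r | D = 0.5 | D = 0.8 | D = 1.0 |
|---|---|---|---|
| 0.3 | 7.1% | 10.3% | 13.7% |
| 0.4 | 8.5% | 14.7% | 20.0% |
| 0.5 | 10.7% | 20.7% | 30.6% |

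With r = 0 the rate is 4.3% to 5.5%. A separate run with 20,000 replicates gave 6.7%, 10.1% and 13.4% for r = 0.3, and 10.6%, 20.7% and 29.5% for r = 0.5. Across repeated runs the low end lay at about 6% to 7% and the high end at about 29% to 31%.

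**If only some cases carry excess dose.** When half of the toxicity group has the higher dose and the rest resemble controls, rejection falls to about 6% (r = 0.3, D = 0.8), 7% (r = 0.4, D = 0.8) and 10% (r = 0.5, D = 1.0).

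**Does adjustment work?** With dose measured without error, rank regression on group plus dose holds 4.6% to 5.4% over all cells with r > 0. With a dose proxy of reliability 0.5 (assumed), about 12% to 13% remains at r = 0.5 and D = 1.0, against about 30% unadjusted.

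**The case against.** The strongest reply is that this contrast is supporting and exploratory. The primary microbiological endpoint is change, which controls cannot show, and the ozone hypothesis rests on the before/after comparison. This stands. A reader might infer that the ozone result or the primary change endpoint is biased by the choice of controls, and the documents do not support that.

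Second, the article promises only an initial comparison of women with and without toxicity, not an effect independent of dose. In the simulation the two groups truly differ in the index, so a rejection is an error only if it is read as specific to toxicity. The article also calls dysbiosis a driver of toxicity. If dose acts through dysbiosis, adjustment may remove part of the difference of interest. This stands too, and it is why the adjusted estimate belongs beside the planned test. Making it the main analysis would be a matter of choice.

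Third, eligibility is pelvic toxicity, which includes bladder and vaginal effects. The article does not say that such cases had more rectal or bowel dose. This weakens the expected imbalance, as the half-case figures show.

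Fourth, the limitations already disclaim causal conclusions, the confounder list is open-ended, and a full protocol or SAP may record radiotherapy variables. The disclaimer, however, cites only design and sample size and does not name dose. The matching factors are a recruitment decision that the article fixes in two places, and recording dose would not by itself change an unadjusted test.

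**Conclusion.** The point holds for the cross-sectional contrast between toxicity and control groups. The article names a factor associated with both group and outcome, then neither matches on it nor adjusts for it. The likely direction is toward more apparent dysbiosis in the toxicity group.

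The size cannot be derived from the documents. Under the assumed correlations (0.3 to 0.5) and dose gaps (0.5 to 1.0 SD), with no dose-independent difference, a nominal 5% test rejects in about 6% to 31% of trials. If half the cases carry no excess dose the range is about 5% to 10%. At the low end the effect is small.

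Two stronger readings go too far. One is that dose drives the dysbiosis and the bias always favors a positive result: section 2 reports correlation and association only. The other is that any group difference found would be an artefact: dose could account for some of it, and the documents do not show that it accounts for all. This is a worthwhile and cheap improvement to a secondary comparison.

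**What to change.** 1. From radiotherapy records, where available, extract for all participants the best measure of rectal or bowel dose, and whether chemotherapy was given.
2. Where several eligible controls exist for a case, prefer the one closest in dose.
3. For single-value microbiota outcomes such as diversity indices, report a group estimate from rank regression on group plus dose beside the planned Mann–Whitney test.
4. State that a proxy such as prescribed dose removes the confounding only in part. If the dose ranges of the groups barely overlap, describe the contrast as toxicity and dose combined.
5. Reconcile the inclusion criterion that accepts radiotherapy and/or chemotherapy with the cohort description in section 5 and with Table 1, so that it is clear whether every control was irradiated.

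The cost is chart abstraction for 38 women and one covariate; no new visits, samples or patients are needed. The documents do not say that dose records are held for everyone, so some values may be missing. Collinearity of dose with group widens the interval. For a gap of D SD the standard error is multiplied by about √(1 + (D²/36)/(2/19)), which is 1.03 at D = 0.5 and 1.12 at D = 1.0, before any gain from the variance that dose explains.
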